
The intersession processes are recorded with the help of the Hartmann and Orlinsky Intersession Questionnaire. The intersession processes are recorded with the help of the Hartmann and Orlinsky intersession questionnaire. In addition to the recording of the processes, it is to be examined in particular to what extent Positive Psychotherapy and Cognitive Behavioral Therapy differ in the therapy processes (intra- and intersession processes) and which variables of both process types predict the therapy success. The control group is not included in the process study. It serves as a comparison group for the effectiveness study in order to examine the effect of a low-threshold Positive Psychology intervention compared to a guided intervention. In order to examine the effect of process variables on therapy outcome (decrease in anxiety symptomatology and general psychosocial distress, increase in happiness experience, life satisfaction and quality of life), two global indicators are formed: 1. frequency and intensity of intra- and intersession activities and 2. emotional valence of intra- and intersession processes (positive vs. negative). The aim of this study is to identify variables of change, to gain knowledge about the therapy processes and thus to optimize the therapy process.

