- 15) The significant increase in life satisfaction and quality of life among patients who participated in the Positive Psychotherapy treatment program remained stable over a period of three months.
- 16) In terms of an exploratory question, it is assumed that the effects of Online Positive Psychotherapy with minimal therapeutic supervision will not remain stable over three months.

The process study will evaluate the process of therapy in Positive Psychotherapy and Cognitive Behavioral Therapy. In the process study, both the intra-session processes and the inter-session processes of therapy with Positive Psychotherapy and Cognitive Behavioral Therapy are to be evaluated. Furthermore, it will be determined which process variables (intra-session or inter-session processes) predict the success of therapy and to what extent Positive Psychotherapy and Cognitive Behavioral Therapy differ in the therapy processes. The intra-session processes will be assessed with the help of the hourly patient assessment form (STU-P). The participants will fill out this questionnaire in digital form after each session. Intersession processes are to be recorded with the help of the Intersession Questionnaire (ISF). The participants fill out this questionnaire in digital form before each session. The aim is to examine and evaluate the process. In this way, it may be possible to make changes to the manuals even after the end of the study and to gain insights into the therapeutic processes. The aim is to identify therapeutic process variables and thus optimize the therapy process.

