#### Research hypotheses:

- 1) Anxiety patients whose intersession activity is emotionally positive show a greater decrease in their anxiety symptoms than patients whose intersession activity is negative. There is a significant correlation between the emotional occupation of the intersession processes and the decrease in anxiety symptoms.
- 2) Anxiety patients whose intersession activity is emotionally positive show a stronger increase in their happiness experience than patients whose intersession activity is negative. There is a significant correlation between the emotional occupation of the intersession processes and the increase in happiness.

- 3) Anxiety patients whose intersession activity is emotionally positive show a greater increase in their life satisfaction and quality of life than patients whose intersession activity is negative. There is a significant correlation between the emotional involvement of the intersession processes and the increase in life satisfaction and quality of life.
- 4) Anxiety patients whose intra-session activity has positive emotional connotations show a greater decrease in their anxiety symptoms than patients whose intra-session activity has negative connotations. There is a significant correlation between the emotional content of the intra-session processes and the decrease in anxiety symptoms.
- 5) Anxiety patients whose intra-session activity is emotionally positive show a stronger increase in happiness than patients whose intra-session activity is negative. There is a significant correlation between the emotional content of the intra-session processes and the increase in happiness.
- 6) Anxiety patients whose intra-session activity is emotionally positive show a higher increase in their life satisfaction and quality of life than patients whose intra-session activity is negative. There is a significant correlation between the emotional occupation of the intra-session processes and the increase in life satisfaction and quality of life.
- 7) Anxiety patients who show a higher level of intersession activity show a greater decrease in their anxiety symptoms at the end of therapy than those who show a lower level of intersession activity. There is a significant positive correlation between the intensity and frequency of intersession activities and the decrease in anxiety symptoms.

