- 8) Anxiety patients who exhibit a higher level of intersession activity show a greater increase in their happiness at the end of therapy than those who exhibit less intersession activity. There is a significant positive correlation between the intensity and frequency of intersession processes and the increase in happiness.
- 9) Anxiety patients who exhibit a higher level of intersession activity show a greater increase in their life satisfaction and quality of life at the end of therapy than those who exhibit less intersession activity. There is a significant positive correlation between the intensity and frequency of intersession processes and the increase in life satisfaction and quality of life.
- 10) Anxiety patients who show a higher level of intra-session activity show a greater decrease in anxiety symptoms at the end of therapy than those who show less intra-session activity. There is a significant positive correlation between the intensity and frequency of intra-session processes and the decrease in anxiety symptoms.
- 11) Anxiety patients who exhibit higher levels of intra-session activity show a greater increase in happiness experience at the end of therapy.

bens, than those who have less intra- session activities. There is a significant positive correlation between the intensity and frequency of intra-session processes and the increase in happiness experience.

12) Anxiety patients who exhibit a higher level of intra-session activity show a greater increase in life satisfaction and quality of life at the end of therapy than those who exhibit less intra-session activity. There is a significant positive correlation between the intensity and frequency of intra-session processes and the increase in life satisfaction and quality of life.

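### Process hypotheses 1-12 are worded as separate correlations, which cannot show which of several possibly related process scores predicts therapy success

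*Protocol*

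**What the plan says.** Section 2.3 of the protocol reduces the process data to two kinds of score: "two global indicators are formed: 1. frequency and intensity of intra- and intersession activities and 2. emotional valence of intra- and intersession processes". The process hypotheses in Section 2.4 (numbered 1 to 12, separately from the efficacy hypotheses) apply each kind to intrasession and to intersession processes, and to three outcome domains: anxiety, happiness, and life satisfaction with quality of life. That gives 2 × 2 × 3 = 12 hypotheses.

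Hypotheses 1-6 concern valence. The first expects that "Anxiety patients whose intersession activity is emotionally positive show a greater decrease in their anxiety symptoms than patients whose intersession activity is negative" and adds the criterion "There is a significant correlation between the emotional occupation of the intersession processes and the decrease in anxiety symptoms". Hypotheses 7-12 concern activity. Hypothesis 7 states: "There is a significant positive correlation between the intensity and frequency of intersession activities and the decrease in anxiety symptoms". Hypothesis 10 has the same form for intrasession processes: "There is a significant positive correlation between the intensity and frequency of intra-session processes and the decrease in anxiety symptoms". None of the twelve mentions another process score, an adjustment or an interaction.

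The aim is comparative. Section 2.3 asks "which variables of both process types predict the therapy success". Section 2.4 says "it will be determined which process variables (intra-session or inter-session processes) predict the success of therapy". Section 2.11 names mixed linear models for change over the measurement points and does not say how process scores enter a model.

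**The concern.** A question about which of several variables predicts an outcome concerns what each contributes once the others are known. A set of one-at-a-time correlations answers a different question: whether each score, taken alone, moves with the outcome. The answers agree when the scores are unrelated and can diverge when they are not.

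Unrelated scores are not a safe default here. They come from the same patients, and within each session type activity and valence come from the same form: the session questionnaire for intrasession processes and the Intersession Questionnaire for intersession processes. A significant activity correlation could therefore be valence seen through activity, or a real activity effect could be hidden. The same holds between intra- and intersession scores.

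The protocol says the findings may lead to changes in the manuals (Section 2.4) and calls the process study the first on this topic in Positive Psychotherapy (Section 2.5). Attributing success to the amount of activity when its tone is what matters would point such changes in the wrong direction.

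**Working it through.** **Inputs from the protocol.** The comparison group is outside the process study (Section 2.3) and each group has 55 subjects (Section 3.5), so n = 2 × 55 = 110 before any loss. Alpha is 0.05 (Section 3.5). Sidedness is not stated; I assume a two-sided test and count significant results in the predicted positive direction, so the reference rate is 2.5%. The protocol gives no power figure for the process study, so there is none to reproduce.

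**Assumed inputs.** The documents give neither the activity-valence correlation, r(A,V), nor any correlation with outcome. I vary r(A,V) from -0.5 to 0.7 and r(V,Y), valence with outcome, from 0.3 to 0.5.

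**Step 1: what the single correlation picks up.** With standardised effects bA (activity) and bV (valence), r(A,Y) = bA + bV × r(A,V). If activity has no effect of its own, bA = 0 and bV = r(V,Y), so r(A,Y) = r(A,V) × r(V,Y). With r(V,Y) = 0.4, this gives 0.3 × 0.4 = 0.12 and 0.5 × 0.4 = 0.20.

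**Step 2: chance of a significant positive result.** By Fisher's z, P = Φ(atanh(r) × √(n - 3) - 1.96), with √107 = 10.34.

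- r = 0.12: 0.1206 × 10.34 = 1.247; Φ(-0.713) = 0.24.
- r = 0.20: 0.2027 × 10.34 = 2.097; Φ(0.137) = 0.55.

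Over the assumed range:

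| r(A,V) | r(V,Y) = 0.3 | r(V,Y) = 0.4 | r(V,Y) = 0.5 |
|---|---|---|---|
| 0 | 2.5% | 2.5% | 2.5% |
| 0.3 | 15% | 24% | 35% |
| 0.5 | 35% | 55% | 75% |
| 0.7 | 60% | 84% | 97% |

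With valence in the model, activity's partial correlation is 0 in every cell and the rate is 2.5%.

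**Step 3: the opposite sign.** At r(A,V) = -0.3 and r(V,Y) = 0.4, r(A,Y) = -0.12. A significant positive result then occurs in about 0.1% of trials and a significant negative one in about 24%.

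**Step 4: masking.** Let activity have a real effect, bA = 0.2, with bV = 0.4 and r(A,V) = -0.5. Then r(A,Y) = 0.2 + 0.4 × (-0.5) = 0.00 and r(V,Y) = 0.4 + 0.2 × (-0.5) = 0.30. The partial correlation of activity given valence is (0 + 0.5 × 0.30) / √((1 - 0.25)(1 - 0.09)) = 0.15 / 0.826 = 0.18. The single correlation has nothing to find; the adjusted test has about 47% power.

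**Step 5: cost of adjusting.** For two predictors correlated 0.5, standard errors grow by 1/√(1 - 0.25) = 1.15. For four scores all correlated 0.5, the variance inflation factor is (1 + 2 × 0.5) / ((1 - 0.5)(1 + 3 × 0.5)) = 2 / 1.25 = 1.6, and √1.6 = 1.26.

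**The case against.** The strongest reply is that these are research hypotheses, not an analysis plan. Covariates and interactions may stand in a statistical analysis plan that is not shown, and Section 2.11 does not prescribe correlations. That is fair, and a missing model is not the point. What remains is that the hypotheses themselves name the criterion, a significant correlation, and it does not match the stated aim. If a joint model is planned elsewhere, the wording should refer to it.

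Second, in the scenario of steps 1 and 2 the marginal correlation really is above zero, so hypothesis 7 as worded is true and its confirmation is no type I error. This also stands. The error would lie in reading that result as showing that activity itself predicts success.

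Third, every correlation used is assumed. At zero there is no problem, and at negative values spurious confirmation all but disappears. The size is therefore conditional, although negative values bring masking instead.

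Fourth, the aim as put in Section 2.4 contrasts session types, not activity with valence. True, but the question in Section 2.3 covers the variables within both types, and the contrast of session types needs joint entry just as much.

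A reader might go further and infer that hypotheses 7-12 contradict 1-6 by treating negative activity as beneficial. They do not: more activity and more positive tone can both go with improvement in an ordinary additive model, and the protocol gives no scoring rule that settles how tone enters the activity score. Nor does it say that negative activity harms. It says only that such patients improve less, so a scenario in which helpful and harmful activity cancel out has no basis in the text.

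**Conclusion.** The point holds in a limited form. The twelve process hypotheses are framed as unadjusted pairwise correlations, while the aim is to say which variables of both session types predict success. Under the assumptions above (n = 110 with no loss, r(V,Y) = 0.4, no effect of activity of its own), hypothesis 7 would be met in 2.5%, about 24% and about 55% of trials at indicator correlations of 0, 0.3 and 0.5. Negative indicator correlations can hide a real activity effect.

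It would be wrong to conclude that the study cannot identify which process variable predicts success. Activity and valence are separate scores on the same patients, so a joint analysis is available from the planned data. The hypotheses as worded do not call for it.

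**What to change.** Keep the twelve correlations and label them as marginal results. For each outcome, add one regression with four scores entered together: activity and valence of intrasession processes, and activity and valence of intersession processes, all centred. State that any claim about which process variable predicts success rests on these mutually adjusted coefficients.

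Treat the activity-by-valence product as an exploratory term. Centring matters for it: with a product in the model, the activity coefficient is the effect at valence zero, which has a useful meaning only if zero is the average valence.

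The cost is some rewording of Section 2.4 and a sentence on the process analysis, with no new data. Precision falls: standard errors are about 15% wider for two predictors correlated 0.5, about 26% for four scores all correlated 0.5, and more once product terms are added.

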## 2.5. Scientific and social relevance (rationale of the project) The scientific

relevance of this study is very high. There are currently only a small number of studies that have investigated the effectiveness of Positive Psychotherapy in clinical patients. Most of the existing

The most recent studies were conducted on patients with depressive disorders. Here, a high efficacy of treatment with positive psychotherapy was found (e.g., Laireiter & Furchtlehner, 2018). The intended study would be the first to examine and comparatively evaluate the effectiveness of the procedures Cognitive Behavioral Therapy and Positive Psychotherapy for Anxiety Disorders in a group setting under online conditions. To the applicant's knowledge, the planned process study is the first ever to have been conducted on this topic in the context of Positive Psychotherapy. Its results can therefore provide important and directional findings with regard to therapeutic processes and changes in Positive Psychology. Also the social relevance is to be estimated as very high. Anxiety disorders are the most common mental disorders of all (Jacobi et al., 2004; Kessler et al., 2005).

According to international studies, lifetime prevalence ranges from 14 to 29% (Kessler et al., 2005; Somers et al., 2006). The quality of life of those affected is very severely limited by their disorder. According to the World Health Organization (WHO), anxiety disorders ranked sixth worldwide and fourth in highly developed (industrialized) countries among all mental and somatic disorders in terms of years lived with disability (YLD) in 2015. Compared to the previous, rather deficit-oriented psychotherapy, Positive Psychotherapy represents a very promising, innovative approach not only to reduce the symptoms, but above all to promote well-being, quality of life and life satisfaction.

## 2.6. Research Design

3x3 variance-analytic within-subjects design (within-subjects: repeated measures factor with three measurement time points: Pre, Post, Follow-up after three months). Between Subjects: Three treatment groups: two online.

conducted intervention and a low-level guided comparison group Controlled intervention study based on written treatment manuals; explicit inclusion and exclusion criteria (see below); rational sample design (see below); randomized patient assignment => RCT.

#### 2.7. Description of the study design (survey time points, type and number of groups, control groups, etc.)

In the following, the procedures used are presented with the common abbreviations; a more precise description can be found below. The study comprises a total of five measurement time points, two screening (pre-selection and telephone/video-assisted interview) and three therapy-related measurements.

1. Online pre-screening for general eligibility using GAD-7, BAI, FQ and PAS and demographic and clinical variables.

2. The second screening takes place in the form of a telephone or video call before the intervention begins. Here, the exclusion criteria are determined by means of

Mini-DIPS and PSS-K are reviewed. In addition, all patients will be informed comprehensively about the course of the study and its contents, and their explicit consent to participate in the study according to the study criteria will be obtained. All participants will also receive the telephone number of the crisis service responsible for their area, so that they can contact them in the event of an emergency.

4. The participants included in the study who meet the inclusion and exclusion criteria will be assigned to one of the three intervention groups (PPT, KVT, minimally supervised PPT). The allocation is randomized. Subsequently, they receive a link to the online questionnaire and complete the questionnaires online to collect the dependent baseline variables (T1). The following self-report questionnaires concerning anxiety are given: Beck Anxiety Inventory (BAI), Panic and Agoraphobia Scale (PAS), Generalized Anxiety Disorder 7 (GAD-7), Social Anxiety and Social Skills Deficits Questionnaire (SASKO), Anxiety Questionnaire (AF)/Fear Questionnaire (FQ), Patient Health Questionnaire.

(PHQ-9), ICD-10- Symptom Rating (ISR) for the assessment of general psychic abnormality. Positive Outcomes: Positive Psychotherapy Inventory (PPTI), Flourishing Scale (FS), Satisfaction with Life Scale (SWLS); External Assessment: Based on the clinical interview, the following procedures are processed by the interviewer: MiniDIPS (mental disorders), PSS-K (personality disorders), SCID PD (personality disorders) Panic and Agoraphobia Scale (PAS) and Hamilton Anxiety Scale (HAMA).

5. The 12-week intervention based on the two manuals is conducted by psychologists in training as clinical psychologists or psychological psychotherapists in a dual trainer setting (two therapists). All therapists are intensively trained in

The group members are trained in the respective manuals, regularly update their work, and also receive regular supervision from experienced representatives of Positive Psychology and Cognitive Behavioral Theory. All group sessions are recorded and discussed in the supervision. Each session is evaluated for its adherence to the manual.

6. Before each therapy session, participants complete the Intersession Questionnaire (ISF) online for process analysis of the therapies, and after each session they complete the Patient Hourly Evaluation Form (STU-P) online.

7. The second questionnaire survey (T2) takes place after the last therapy session. For this purpose, the participants are sent the link to the online survey again. The same self-assessment procedures are used as for T1. This time, too, there will be an external assessment. This is done by the therapists using the Panic and Agoraphobia Scale (PAS) and the Hamilton Anxiety Scale (HAMA).

8. Three months after the end of the online groups, the participants receive another email with a link and a request to complete the questionnaire battery (=Follow-Up, T3). This time, too, the same self-assessment procedures are given as in T1 and T2. At this point of measurement, no further external assessment takes place.

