## 2.8. Description of the methods of data collection, instruments

As can be seen from the previous section, both self-assessment and external assessment procedures are integrated into the data collection. In both cases, psychometrically tested clinical interviews and scales are used. The collected characteristics of the efficacy study are divided into primary and secondary outcomes and include anxiety expression as well as additional psychopathological characteristics.

Personal and socio-demographic data:

- Name, place of residence, e-mail address, telephone number; age, gender, marital status, education, nationality.

Screening and diagnostics:

- MiniDIPS: (current and lifetime) diagnoses of mental disorders
- PSS-K: Personality Disorder Screening Short Form
- SCID PD: Structured Clinical Interview-Personality Disorders (for indications according to PSS-K).
- Other clinical data: psychometric data from clinical procedures, psychiatric treatment, use of psychotropic drugs, past psychotherapy/s (number, type).

Primary Outcomes:

1. Anxiety Symptomatology:

|                                             |                     |
|---------------------------------------------|---------------------|
| Self-assessment                             | BAI, PAS; GAD-7, FQ |
| External assessment                         | PAS, HAMA           |
| 2. positive outcome                         |                     |
| Positive Psychotherapy                      | PPTI                |
| Inventory Flourishing Scale                 | FS                  |
| Satisfaction with Life-Scale                | SWLS                |
| Secondary Outcome:                          |                     |
| ICD-10 Symptom Rating                       | ISR                 |
| Patient Health                              |                     |
| onnairePHQ-9                                | Questi              |
| Process Study:                              |                     |
| Hourly assessment questionnaire me patients |                     |

STU-P Interession questionnaire ISF

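### Clinician-rated PAS and HAMA are primary outcomes, but the rater role changes from interviewer at T1 to therapist at T2, so rater and time are confounded for these two measures

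*Protocol*

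**What the plan says.** Section 2.8 puts two kinds of anxiety measure under "Primary Outcomes": self-assessment (BAI, PAS, GAD-7, FQ) and external assessment (PAS, HAMA).

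Section 2.7 fixes who makes the external ratings:

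- **T1 (step 4):** "Based on the clinical interview, the following procedures are processed by the interviewer", and the list that follows includes "Panic and Agoraphobia Scale (PAS) and Hamilton Anxiety Scale (HAMA". The interview is step 2, before allocation: "The second screening takes place in the form of a telephone or video call before the intervention begins".
- **T2 (step 7):** "This is done by the therapists using the Panic and Agoraphobia Scale (PAS) and the Hamilton Anxiety Scale (HAMA". Step 5 of the same section describes the intervention as "conducted by psychologists in training as clinical psychologists or psychological psychotherapists in a dual trainer setting (two therapists", so therapists here means the people who deliver the groups.
- **T3 (step 8):** "At this point of measurement, no further external assessment takes place".

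The protocol describes no assessor who is independent of treatment or blind to arm, no common rater at T1 and T2, and no check of agreement between raters.

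**The concern.** Who scores a primary outcome is a design matter that this protocol settles itself, and it settles it differently at the two time points. A therapist's rating may sit lower or higher than an interviewer's for the same patient. Any such gap goes straight into the pre-post change.

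At stake are the within-arm hypotheses 1 (PPT) and 3 (cognitive behavioural therapy, KVT in the protocol), as far as they are judged on HAMA or external PAS. If the gap also differs between arms, the arm contrasts on these scales are exposed as well. Section 2.4 names no instrument for any hypothesis, so nothing stops a primary claim from resting on these two scales.

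**Working it through.** **1. Rater role against time.**

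| Measure | T1 | T2 | T3 |
|---|---|---|---|
| External PAS, HAMA | interviewer | therapists | none |
| BAI, self-rated PAS, GAD-7, FQ | participant | participant | participant |

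In the first row, role and time change together for everyone. The mixed model in section 2.11 cannot separate them, with or without a rater term, because no participant has a therapist rating at T1 or an interviewer rating at T2.

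**2. Which hypotheses are exposed on the external scales.** Write the rater shift in arm *a* as b_a, in SD units of a single rating.

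- Within arm (hypotheses 1 and 3): observed change = true change + b_a. The bias is the whole shift.
- Between arms: bias = b_a − b_c. A shift common to both arms cancels.
- PPT or KVT against control (hypotheses 2 and 4): a differential shift is plausible. Therapists deliver the treatment and so presumably know the arm. Section 2.3 gives the control arm 3 online group sessions out of 12, against 12 group sessions plus one individual session in each active arm.
- PPT against KVT (hypothesis 5): contact is the same in both arms, so only differential allegiance remains. The practitioner criteria in section 3.28 ask for coursework in positive psychology and name none in KVT. That makes allegiance conceivable but gives neither its direction nor its size.
- Stability to T3 (hypotheses 12 and 13): the external scales contribute nothing, because they are not collected at T3.

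**3. Illustration of size.** The protocol has no figure on this point to reproduce. Inputs: n = 55 per arm and α = 0.05 (section 3.5), with the test taken as two-sided because the section does not say. Assumptions: no true effect, shift b of 0.1 to 0.3 SD, T1–T2 correlation ρ of 0.3 to 0.7.

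- SD of change = √(2(1−ρ)) = 1.183, 1.000, 0.775 for ρ = 0.3, 0.5, 0.7
- SE within arm = SD of change / √55
- SE between arms = SD of change × √(2/55)
- Rejection rate = 1 − Φ(1.96 − b/SE) + Φ(−1.96 − b/SE)

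Worked case, b = 0.3 and ρ = 0.5:

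- Within: SE = 1/7.416 = 0.135, b/SE = 2.22, rejection 60.4%.
- Between: SE = 0.191, b/SE = 1.57, rejection 35.0%.

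| Shift b | Within arm, ρ = 0.3 / 0.5 / 0.7 | Between arms (b = difference in shift), ρ = 0.3 / 0.5 / 0.7 |
|---|---|---|
| 0.1 SD | 9.6 / 11.5 / 16.0% | 7.3 / 8.2 / 10.4% |
| 0.2 SD | 24.1 / 31.7 / 48.2% | 14.4 / 18.2 / 27.3% |
| 0.3 SD | 46.8 / 60.4 / 81.9% | 26.5 / 35.0 / 52.8% |

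For scale, section 3.5 plans for a between-group effect of d = 0.15 to 0.30. A differential shift of 0.2 to 0.3 SD would be as large as the effect being sought.

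**The case against.** The case on the other side has several parts.

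- **Own-group rating and change of person are not stated.** A reader might infer that each therapist rates their own patients and that a different person rated them at T1. Step 7 says only that the therapists rate, and step 4 does not say who the interviewer is; it could be one of the study psychologists. This stands. What is documented is a change of role. Knowledge of the arm is a fair inference from delivering the treatment, but still an inference.
- **Only two entries are affected.** This stands. The self-reports, including PPTI, FS and SWLS for the positive outcomes, are given in the same way at all three time points.
- **The missing T3 rating is openly stated.** This stands. The scales can be analysed over T1 and T2, and one clarifying sentence is enough.
- **Less contact need not mean less information.** The protocol does not say whether T2 ratings rest on a fresh interview or on session impressions. This weakens the contact argument for hypotheses 2 and 4 but does not remove it.
- **The shift is assumed.** This stands. At 0.1 SD and ρ = 0.5 the rejection rates are only about 12% within an arm and 8% between arms.

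None of this answers the central fact: for two declared primary measures the rater role changes exactly when the effect is measured, and nothing in the protocol prevents own-group rating.

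**Conclusion.** The point holds for external PAS and HAMA. On these scales rater role is confounded with time for hypotheses 1 and 3. A differential shift could bias hypotheses 2 and 4, and for hypothesis 5 only differential allegiance is left. Under the assumptions above, shifts of 0.2 to 0.3 SD give false rejection in about 24 to 82% of within-arm tests and 14 to 53% of between-arm tests. These figures show sensitivity; the protocol gives no value for the shift or the correlation.

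A reader might go further and conclude that the primary anxiety result cannot be interpreted, or that hypotheses 12 and 13 cannot be tested. The document does not support either conclusion. The self-reported primaries do not change rater and can test hypotheses 1 to 5, 12 and 13. They are not blinded either, but they do not have this fault. Only a claim resting on the two external scales alone would be undermined. Severity: should fix.

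**What to change.** 1. In section 2.8, move external PAS and HAMA from primary to secondary and keep the self-report anxiety measures as primary.
2. State there that the external ratings cover T1 to T2 only and are not blinded, and that the rater role differs between the two time points if that remains so.
3. Where existing staff allow, have T2 rated by the same interviewer pool as T1, or at least by someone who did not lead the participant's group. Do not claim blinding to arm unless it can be kept: therapists discuss sessions in shared intervision and supervision, so a swapped therapist may well know the arm.

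Steps 1 and 2 are wording changes. Step 3 needs some rota work and, if interviewers are used, rating time for up to 165 participants in a project without funding (section 2.14). It has to be arranged before T2, because an independent rating cannot be recovered later. The price of step 1 is that clinician ratings no longer carry a primary claim.
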